#### **Eligibility**

##### *Eligibility criteria for clusters*

Village clinics with an annual outpatient volume exceeding 2000, an average of 10 or more patients per week presenting with ARIs, and licensed prescribers are considered eligible for selection for the intervention. Annual outpatient prescriptions and average weekly visits for ARIs will be verified by obtaining prescription data from all village

clinics for the previous year, as documented in the information section of the local health board.

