### **Sample size**

Based on our exploratory study and previous research, the antibiotic prescription rate in rural primary healthcare institutions in China ranges from 50% to 80%. The minimum value of 50% is utilised as a conservative estimate of the conventional antibiotic prescription rate in the control arms. We conservatively estimate that CRP&SAA POCT intervention will lead to at least a 25% relative reduction in the antibiotic prescription rate in village clinics. Thus, to detect a reduction of 25% or more in the antibiotic prescription rate - specifically, an absolute reduction to 37.5% antibiotic prescription rate or lower - with 90% power, utilizing two-sided testing at the 5% significant level, and assuming a harmonic mean cluster size of 500 along with an intracluster correlation coefficient of 0.05, we estimate that we will require 17 village clinics per arm. Allowing for a 15% loss of prescription data and considering that 20 village clinics are required per arm, it was decided to include a total of 40 village clinics.

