### **Data analysis plan**

All analyses will be conducted on the intention-to-treat (ITT) population, defined as all outpatient prescriptions issued by village clinics for ARI patients, regardless of the compliance of village doctors and patients with the intervention. For the primary and secondary outcomes, which are binary variables, we will employ Generalised estimating equations (GEEs) to estimate both relative and absolute measures of effect. The same methods will be used to analyse the mean cost of an ARI prescription and a consultation. The primary outcome will also be analysed in subgroups based on ARI

patient's age (1-15 / 16-65 / over 65 years old), ARI patient's sex (male / female), type of ARI (upper respiratory tract infection / lower respiratory tract infection), and season. Likelihood ratio tests will be employed to assess the heterogeneity of antibiotic prescribing across these different subgroups. We also will conduct per-protocol analyses, which included only ARI patients who received CRP&SAA POCT in village clinics within the intervention arm. Furthermore, modified poisson regression and linear regression models, which account for village-level clustering using the clustered sandwich estimator, will be employed to replicate all results and assess their robustness. No interim analyses are planned, and all outcomes will be analysed following data collection.

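### The primary GEE is described without a baseline term, although previous-year prescription data are obtained that could supply one; pre-specifying it would cost little and could narrow the interval

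*Protocol*

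**What the plan says.** The Data analysis plan states for the binary outcomes that "we will employ Generalised estimating equations (GEEs) to estimate both relative and absolute measures of effect". It goes on to subgroups, a per-protocol set, and modified Poisson and linear regression as robustness models. No covariate is named for any of these models, neither a baseline prescribing rate nor the township stratum. Adjustment is not ruled out either.

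Under Eligibility criteria for clusters, outpatient volume and weekly ARI visits "will be verified by obtaining prescription data from all village" clinics for the previous year, held by the local health board. That section uses the data for these two counts only and does not mention antibiotic content. The Primary outcome section says that prescriptions are now stored electronically.

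The Sample size section plans "with 90% power, utilizing two-sided testing at the 5% significant level", with a control rate of 50% and "an absolute reduction to 37.5% antibiotic prescription rate or lower" under intervention, "assuming a harmonic mean cluster size of 500 along with an intracluster correlation coefficient of 0.05". It concludes "we estimate that we will require 17 village clinics per arm", raised to 20 for loss of data. Allocation is stratified by township.

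**The concern.** With about 500 prescriptions per clinic and only 40 clinics, almost all the uncertainty about the effect comes from clinics differing in their prescribing habits. More prescriptions per clinic barely help. What can help is a clinic-level variable that predicts the trial-period rate, and the clinic's own recent ARI antibiotic rate is a natural candidate. The source data appear to be in hand before randomisation, since they are needed to decide which clinics are eligible.

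If the model is fitted without this variable, the interval may be wider than it needs to be, and a chance difference in prescribing habit between the two groups of 20 clinics stays in the estimate. If the adjustment is first chosen after outcomes are seen, it loses credibility. The case for fixing it in advance is therefore one of efficiency and pre-specification.

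**Working it through.** **Inputs from the Sample size section:** p1 = 0.50, p2 = 0.375, two-sided 5%, 90% power, m = 500, ICC = 0.05, 15% loss. **Assumed, not in the documents:** the correlation c between a clinic's underlying rates in the previous year and in the trial; 500 usable baseline records per clinic (with 1,000 the results barely change).

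**1. The plan's own figure.** Design effect = 1 + 499 × 0.05 = 25.95. Individuals per arm without clustering = (0.25 + 0.234375) × (1.960 + 1.282)² / 0.125² = 325.7. Clinics per arm = 325.7 × 25.95 / 500 = 16.9, so 17. Allowing for loss, 17 / 0.85 = 20. The stated numbers reproduce, and they do not rely on adjustment.

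**2. Where the variance lies.** Between-clinic share of the variance of a clinic's observed rate = m × ICC / design effect = 25 / 25.95 = 0.963.

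**3. Unadjusted precision, 20 clinics per arm.** SE = √(0.484375 × 25.95 / (20 × 500)) = 0.0355. Half-width = 2.024 × 0.0355 = 7.2 points (t, 38 df). Power at 12.5 points from the noncentral t is 93% (94% from the normal approximation).

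**4. With a clinic-level baseline covariate.** The correlation of observed rates is r = c × 0.963, and the variance of the effect is multiplied by 1 − r². Half-widths and power use 37 df.

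| c (assumed) | r | Variance reduction | Half-width (points) | Power at 12.5 points |
|---|---|---|---|---|
| none | – | – | 7.2 | 93% |
| 0.3 | 0.289 | 8.4% | 6.9 | 95% |
| 0.5 | 0.482 | 23.2% | 6.3 | 97% |
| 0.7 | 0.674 | 45.5% | 5.3 | 99.6% |
| 0.8 | 0.771 | 59.4% | 4.6 | >99.9% |

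At c = 0.7 the SE is about 2.6 points, equivalent to 1 / 0.545 = 1.8 times as many clinics.

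**5. Cost if the covariate is useless.** Estimating one slope inflates the SE by about √(1 + 1/36) = 1.014. With the slightly larger t quantile (2.026 against 2.024) the interval widens by about 1.5%. The table leaves this inflation out; including it adds about 0.1 point to each adjusted half-width.

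**6. A diluted effect, for illustration.** At an 8-point reduction (50% to 42%) the unadjusted SE is √((0.25 + 0.2436) × 25.95 / 10,000) = 0.0358 and power is about 59%. At c = 0.7, with the inflation in step 5, power is about 83%.

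**7. Chance imbalance.** The ICC at a 50% rate implies a between-clinic SD of √(0.05 × 0.25) = 0.112. The difference between two means of 20 clinics then has SD 0.112 × √(2/20) = 0.035, so a gap of 5 points or more in underlying prescribing arises about 16% of the time, before any benefit from township stratification.

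None of these steps models township.

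**The case against.** The strongest reply is that covariate lists usually belong in the SAP, which is not at hand, and that the protocol is silent on adjustment. A reader might infer that the trial has decided on an unadjusted analysis, or that such an analysis would be invalid. The document supports neither: it names a model family and excludes nothing, and an unadjusted GEE remains a legitimate analysis under randomisation. What survives is narrower. The protocol describes its primary and robustness models with no baseline term while obtaining data that could provide one, and the change is concrete and nearly free.

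Other stronger readings also go beyond the documents:

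- **That the trial is underpowered without adjustment.** Power at the design effect is about 93%. The 8-point figure is illustrative. Dilution is plausible, because testing is recommended rather than required, patients may decline it, and the analysis is by intention to treat. The protocol does not plan for an 8-point effect.
- **That the gain is certainly large, or equals doubling the clinics.** It depends on a correlation the documents do not give. It is small at 0.3 and moderate at 0.5; at 0.7 it equals about 1.8 times the clinics.
- **That the 50% to 80% range shows the spread among these 40 clinics.** It describes rural institutions in China generally and serves to choose the control rate: "The minimum value of 50% is utilised as a conservative estimate of the conventional antibiotic prescription rate in the control arms". The plan's measure of spread between clinics is the ICC.
- **That the baseline rate is already available.** The eligibility section does not say that antibiotic content is extracted, or that the 14-day initial-visit definition can be applied to last year's records. Availability before randomisation is inferred from the eligibility step.

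Township is a fair objection and stands. Stratification already limits some imbalance. The 40 clinics are spread over 15 + 4 = 19 areas, about two per area, so township terms could absorb part of the same variance and would use many degrees of freedom.

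**Conclusion.** The point holds as an efficiency recommendation. Under the plan's ICC and cluster size, 96% of the variance of a clinic's rate is between clinics, so a clinic-level baseline covariate is the main remaining source of precision. The size of the gain is a range, from a few tenths of a point off the half-width at a correlation of 0.3 to more than 2.5 points at 0.8. It rests on three assumptions: the year-to-year correlation, an extract that identifies antibiotics on ARI prescriptions, and no overlap with township. The trade is asymmetric, about 1.5% lost if the covariate predicts nothing. No stated figure is wrong and nothing in the protocol is contradicted.

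**What to change.** Before outcome data are seen, confirm that the previous-year extract can flag antibiotics on ARI prescriptions. If it can:

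- pre-specify each clinic's previous-year ARI antibiotic prescribing proportion as a covariate in the primary GEE;
- decide in the same place how township, the randomisation stratum, enters the model;
- obtain the absolute and relative effects from this model by standardisation;
- keep the unadjusted model as a sensitivity analysis.

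The cost is one clinic-level variable computed from data already being obtained, one degree of freedom, and a sentence or two in the analysis plan. The sample size need not change. If the SAP already specifies this adjustment, nothing more is needed than to bring the protocol's description into line.

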#### *Eligibility criteria for participants*

The target population of this study included (1) patients of all ages diagnosed by a village doctor with ARIs (including upper and lower respiratory infections); and (2) patients who present with  $\geq 1$  acute respiratory symptoms (including cough, rhinitis (sneezing, nasal congestion or runny nose), sore throat, shortness of breath, wheezing or abnormal auscultation). Patients with non-respiratory diseases or those with severe clinical symptoms requiring referral to a higher-level institution are excluded from the target population.

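### Subgroup heterogeneity is to be tested by likelihood ratio, but no model named in the protocol has a likelihood that accounts for clinic clustering; a test that ignores clinics can over-declare subgroup effects

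*Protocol*

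**What the plan says.** The Data analysis plan names one main method: "we will employ Generalised estimating equations (GEEs) to estimate both relative and absolute measures of effect". The same method serves for the cost means. As a robustness check it adds "modified poisson regression and linear regression models, which account for village-level clustering using the clustered sandwich estimator".

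The primary outcome is then broken down by patient "age (1-15 / 16-65 / over 65 years old"), sex, "type of ARI (upper respiratory tract infection / lower respiratory tract infection), and season". The test for these breakdowns is given in one sentence: "Likelihood ratio tests will be employed to assess the heterogeneity of antibiotic prescribing across these different subgroups". I read it as a test of whether the intervention effect differs between subgroups, that is, of the arm-by-subgroup interaction. The protocol names no mixed-effects or other full-likelihood model for clustered data, and does not say which model the likelihood ratio test comes from.

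The participant eligibility criteria admit "patients of all ages diagnosed by a village doctor with ARIs".

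**The concern.** A likelihood ratio test compares the maximised likelihoods of two nested models. A GEE solves estimating equations under a working correlation and maximises no likelihood, so the named test cannot be taken from the named model. The modified Poisson and linear models do have a working likelihood, but it treats visits as independent. The clustered sandwich repairs their standard errors and leaves that likelihood unchanged.

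An analyst who follows the text literally may therefore refit a regression that ignores clinics and report its likelihood ratio p-value. The trial is planned around strong clustering, so a statement that the intervention works differently by age, sex, season or ARI type could rest on a p-value that is too small.

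Two smaller points sit in the same subgroup plan. The age bands leave out infants under 1 year. And ARI type is recorded after randomisation by doctors who know their arm.

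**Working it through.** **Inputs from the protocol (Sample size).** Control rate 50% ("The minimum value of 50% is utilised as a conservative estimate of the conventional antibiotic prescription rate in the control arms"), intervention rate 37.5%, two-sided 5%, power 90%, cluster size 500, ICC 0.05, 17 clinics per arm before loss and 20 after.

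**The plan's own figure.** Design effect = 1 + 499 × 0.05 = 25.95. Visits per arm under independence = (1.96 + 1.2816)² × (0.25 + 0.2344) / 0.125² = 325.7. Clinics per arm = 325.7 × 25.95 / 500 = 16.9, so 17; and 17 / 0.85 = 20. The stated numbers reproduce. The protocol gives no figure for the subgroup test.

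**When ignoring clinics does no harm.** All four subgroup factors vary within a clinic. With a common clinic effect and the same mix everywhere, that effect cancels from the subgroup contrast. The true variance is then 1 − 0.05 = 0.95 of the naive one, and the type I error is 2 × [1 − Φ(1.96/√0.95)] = 4.4%.

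**When it does harm.** Take two equal subgroups, so 20 × 250 = 5,000 visits per arm-by-subgroup cell. The naive variance of the interaction log odds ratio is 2/(5,000 × 0.25) + 2/(5,000 × 0.375 × 0.625) = 0.00331. Two kinds of between-clinic variation add to the true variance without entering the naive one.

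- *Mix.* If the subgroup share has between-clinic SD s and clinic intercepts have logit variance v, the added variance is approximately 2 × v × s² / (0.25² × 20). An ICC of 0.05 on the latent scale gives v = (0.05/0.95) × π²/3 = 0.173. With s = 0.10 the addition is 0.00277, the variance ratio is 1 + 0.00277/0.00331 = 1.84, and the type I error is 2 × [1 − Φ(1.96/√1.84)], about 15%. With s = 0.05 the ratio is 1.21 and the error about 7.5%. With s = 0.20 they are 4.35 and about 35%. This first-order formula runs a little high at large s.
- *Clinic-by-subgroup deviations.* If the subgroup difference has between-clinic SD 0.2 on the logit scale, the addition is 2 × 0.04/20 = 0.004, the ratio 2.21 and the error about 19%. If 0.2 is instead the SD of each subgroup's own deviation, the difference has twice that variance, the ratio is 3.42 and the error about 29%.

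**Simulation.** No true interaction, 20 clinics per arm, 500 visits each, 3,000 or 4,000 trials per setting. Rejection rate at nominal 5% of an ordinary logistic likelihood ratio test, with ranges across runs:

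| Assumed between-clinic variation | Type I error |
|---|---|
| None (2 levels; 3 levels) | 4.5-5.5%; 5.2% |
| Mix SD 2; 3; 5 points | 5.0%; 5.4%; 7.2% |
| Mix SD 10 points | 12.8-14.2% |
| Mix SD 20 points | 30.4-32.5% |
| Clinic-by-subgroup SD 0.2 | 18.4-27.7% |
| Mix SD 10 plus clinic-by-subgroup variation | 23.6-24.3% |

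The two ends of the 18.4-27.7% range match the two readings of SD 0.2 worked above. With clinic variance 0.2 in place of 0.173, mix SDs of 11, 15 and 22 points gave 16.5%, 25.9% and 38.1%. When each subgroup has its own deviation with SD 0.1 or 0.3, the rate was 11.6% or 41.2%. A Poisson likelihood, as in the robustness model, gave 0.9% with equal mix and 19.0% at mix SD 20, so the answer also depends on which likelihood is picked. A cluster-robust Wald test with small-sample correction and t reference stayed at 4.4-5.2%.

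**Age bands.** All ages are eligible, while the youngest band starts at 1, so a patient under 1 year falls in no band.

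**ARI type.** Under Allocation and blinding, doctors know their arm. Under Healthcare worker training, intervention doctors are trained in the clinical evaluation of ARIs. Under Usual care, control doctors get no such education. The upper/lower label can therefore shift by arm.

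**The case against.** The strongest reply is that nothing in the protocol says the test will come from a model that ignores clinics. A logistic model with clinic random effects has a proper likelihood, and robust corrections to working likelihood ratio statistics exist for GEE. A reader might infer that an ordinary regression is the only route to the statistic; that is not so. One may add that the source model is a detail for a statistical analysis plan. This stands in part. However, the protocol does more than leave the model open: it names the models and it names the test, and they do not fit together.

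A second reply is that over-declaration is not shown. On the protocol's own ICC and cluster size, with equal mix, the ordinary logistic test holds its level. All clinics lie in one city and the trial lasts six months, so a mix SD of 10 to 20 points for sex or season is hard to argue. At 2 to 5 points, the excess due to mix is at most about 2 percentage points. This also stands. A reader might infer that the test will over-declare; the documents support only that it can. Age and ARI type are likelier to differ between clinics, since the clinics span 19 townships and sub-districts and each has one or two doctors making the diagnosis. Clinic-by-subgroup deviations could affect any of the four factors.

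Third, a reader might infer that ARI type is labelled after the doctor has seen the test result. The protocol does not say when the label is recorded relative to testing. The caution rests only on unblinded labelling and training given to one arm.

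**Conclusion.** The mismatch between model and test is real and stands in the protocol's text. If the test is taken from a logistic regression that ignores clinics, its type I error runs from about 5% with no between-clinic variation in mix or contrast to about 30-32% at a mix SD of 20 points, and to 18-28% with clinic-by-subgroup deviations of SD 0.2 on the logit scale. The size therefore rests on assumed variation for which the documents give no figure.

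This should be fixed, but it is not critical. The primary estimate and its test, the sample size, the secondary outcomes and the safety indicator are unaffected. The age-band gap is minor: infants under 1 year stay in the primary analysis and drop out of one subgroup table only.

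**What to change.** Replace the sentence on likelihood ratio tests with wording such as: *Heterogeneity of the intervention effect will be assessed by a joint robust Wald (or generalised score) test of the arm-by-subgroup interaction within the GEE clustered by clinic, using a small-sample-corrected covariance and a t or F reference suited to 40 clinics.* If a likelihood ratio test is preferred, name the mixed model it comes from, with clinic random effects and, where needed, clinic-by-subgroup effects.

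Start the youngest age band at 0. Add a line that the ARI-type subgroup is to be read with caution, because the label is assigned after randomisation by unblinded doctors of whom only one arm is trained in ARI evaluation.

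The cost is one replaced sentence, one changed age limit and one added line, with no new data. Fewer subgroup results may reach nominal significance.

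### Subgroup heterogeneity is to be tested by likelihood ratio, but none of the models the protocol names (GEE, or regression with a clustered sandwich) gives a valid likelihood ratio for clustered data

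*Protocol*

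**What the plan says.** All the analysis statements are in the protocol's Data analysis plan.

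- Main model: "we will employ Generalised estimating equations (GEEs) to estimate both relative and absolute measures of effect".
- Subgroups of the primary outcome: age in three bands, sex, and "type of ARI (upper respiratory tract infection / lower respiratory tract infection), and season".
- Heterogeneity between these subgroups: "Likelihood ratio tests will be employed to assess the heterogeneity". The model that supplies the likelihood is not named.
- Robustness: modified Poisson and linear regression, "which account for village-level clustering using the clustered sandwich estimator", used to replicate the results.

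No mixed model or other likelihood that accounts for clinics is named. The clinic is the randomised unit (Allocation and blinding), and the Sample size section plans on clustering, "assuming a harmonic mean cluster size of 500 along with an intracluster correlation coefficient of 0.05".

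**The concern.** A likelihood ratio test compares maximised likelihoods. A GEE solves estimating equations and has none. Modified Poisson and linear regression do maximise a function, but it is the likelihood of independent patients. The clustered sandwich changes the standard errors afterwards and leaves the likelihood ratio as it was. The test and the models therefore do not fit together, even when the hypothesis is taken, properly, as an arm-by-subgroup interaction.

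This is more than detail left to an SAP. The protocol positively names a test, and an SAP that keeps both the test and the named models would have to ignore clinics. At stake is whether a reported difference in effect, for example between upper and lower ARI, reflects a real difference or only variation between clinics.

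**Working it through.** **1. The plan's own figure.** No error rate is stated for the subgroup test, so the sample size inputs were checked instead: 50% v 37.5%, "with 90% power, utilizing two-sided testing at the 5% significant level", 500 patients per clinic, ICC 0.05.

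- n per arm = (1.960 + 1.282)² × (0.5×0.5 + 0.375×0.625) / 0.125² = 10.507 × 0.484375 / 0.015625 = 325.7
- Design effect = 1 + 499 × 0.05 = 25.95
- Clinics per arm = 325.7 × 25.95 / 500 = 16.9, so 17; and 17 / 0.85 = 20

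This reproduces the plan's 17 and 20.

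**2. Assumed inputs.** A clinic intercept SD of 0.447 logits corresponds to the planned ICC at 50%: 0.447² × 0.25 = 0.05. The documents do not say how far clinics differ in subgroup mix, or in the gap in prescribing between subgroups. Those SDs (logit scale) are assumptions and were varied.

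**3. Why the ICC alone does no harm.** The interaction is largely a within-clinic contrast. If every clinic has the same mix and the same gap, the clinic effect cancels and the ordinary test holds its level.

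**4. Hand calculation for a varying gap.** At a 50% rate, the sampling variance of one clinic's gap in log odds is v = 1/(n₁×0.25) + 1/(n₂×0.25).

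- 80/20 split (400 and 100): v = 0.01 + 0.04 = 0.05
- Equal split (250 and 250): v = 0.016 + 0.016 = 0.032

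If the gap varies with SD τ, the true variance exceeds the assumed one by the factor r = 1 + τ²/v. The actual two-sided error is then P(|Z| > 1.96/√r).

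| Split | τ | r | Hand result | Simulated |
|---|---|---|---|---|
| 80/20 | 0.2 | 1.80 | 14% | 13% |
| 80/20 | 0.3 | 2.80 | 24% | 21% |
| 80/20 | 0.5 | 6.00 | 42% | 39% |
| Equal | 0.2 | 2.25 | 19% | 19% |
| Equal | 0.3 | 3.81 | 32% | 30% |

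**5. Simulation.** 40 clinics of 500, no true interaction, no arm effect, 20% lower ARI (unless stated as equal), nominal 5%, 2,000 trials per scenario. It compared an ordinary logistic likelihood ratio test with a clinic-robust Wald test on 38 df.

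- Identical mix and gap: 6%
- Mix SD 0.5 or 1.0: 13% or 32%
- Gap SD 0.2, 0.3 or 0.5: 13%, 21% or 39% (right-hand column above)
- Mix SD 1.0 with gap SD 0.5: 52%
- Clinic-robust Wald test: 4% to 6% throughout

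Repeat simulations on the same set-up put the top scenario at 54% to 55% and the robust test at up to 7%. A separate simulation, with an arm effect of the planned size and other forms of between-clinic variation, gave 4.8% to 5.9% for the ordinary test when nothing varied. When mix or subgroup-specific prescribing varied, it gave 8% to 69%. The robust test with an F reference gave 4.5% to 6.2%.

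**6. Dependence on the working likelihood.** A Poisson likelihood overstates the variance of a binary outcome (p instead of p(1−p)), so its likelihood ratio is conservative. In the same kind of scenario:

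| Scenario | Poisson | Logistic |
|---|---|---|
| Identical mix and gap | 0.5% | 4.5% |
| Mix SD 0.5 | 4.5% | 15% |
| Gap SD 0.2 | 3.5% | 13% |
| Gap SD 0.3 | 8% | 22% |

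Poisson inflation returns in the wider scenarios: 17.5% at mix SD 1.0, 21% at gap SD 0.5, 40% with both. Linear regression was not simulated.

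**7. Clinic intercepts only.** Giving each clinic its own intercept removed the inflation from a varying mix (5% to 6%) but not from a varying gap (13%, 21% and 40% at SD 0.2, 0.3 and 0.5).

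**The case against.** Several points on the other side stand.

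- A reader might infer that clinics will be ignored. The protocol does not say so. It leaves the model behind the test unnamed, and a mixed model could supply a valid likelihood ratio. What the document shows is a mismatch of test and model.
- A reader might infer that false subgroup findings far above 5% are certain. With the only inputs the protocol gives, 500 per clinic and ICC 0.05, the ordinary test stays near 5%. All inflation comes from assumed variation between clinics.
- The main magnitudes are for a logistic likelihood, which the protocol does not name. For the named Poisson model the mild scenarios show no material inflation, and the identical-clinic case is well below 5%.
- The variation is not equally plausible for all four factors. All clinics share one six-month period, so seasonal mix is largely set by the calendar, and nothing suggests large differences in sex mix. The case is strongest for ARI type, which is diagnosed by the village doctor, in clinics with one or two doctors each.

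One defence stands in part. The robustness models are to replicate all results, so clinic-robust interaction estimates may exist to set beside the likelihood ratio tests. That would help interpretation, but it leaves the stated heterogeneity test as it is.

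**Conclusion.** Wrong as written; it should be fixed, and it concerns the subgroup analyses only. The named test cannot be validly formed from any model the protocol names, and that follows from the text without any simulation.

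The size of the consequence is conditional. On an ordinary logistic likelihood with 40 clinics of 500, the false-positive rate is about 5% if clinics are alike in subgroup mix and gap, and about 13% to 55% under the assumed variation used here. Other working likelihoods give smaller or different figures. The documents give no between-clinic SDs, so no single figure can be attached to this trial.

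The primary test, the sample size and the safety indicator are untouched. It might also be inferred that a false subgroup result would shape the policy briefs. The Dissemination section plans such briefs but ties none of them to subgroups, so that does not follow.

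**What to change.** Replace the likelihood ratio sentence. Fit an arm-by-subgroup interaction in the same GEE as the primary analysis, and test it by a clinic-robust Wald or generalised score test against a t or F reference with clinic-level degrees of freedom (38 for 40 clinics in two arms).

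If a likelihood ratio test is preferred, name its model: a mixed model with a random clinic effect and a random clinic-by-subgroup effect. A clinic intercept alone is not enough when the subgroup gap varies between clinics.

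The cost is one sentence in the protocol, the same in the SAP, and a few lines of code. The downside is that fewer subgroup p-values may reach significance.
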